### Participant allocation

Numbered, identical, opaque sealed envelopes will be used for patient allocation in the current trial. The allocation envelope contains the treatment allocation card showing either group 1 or group 2. The allocation envelopes will be kept in a labelled box in an agreed location in the clinical environments. After the clinician obtains informed consent from the patient, a dental nurse will be asked to identify the next allocation envelope in sequence. The allocation will only be revealed at the time of appliance placement. Then the allocation envelope will be opened in front of the participant. Both the participant and the clinician will be informed about the group allocation for the participant.

### Blinding

Due to the nature of the trial it is not possible to blind the clinician to the group once it is allocated. Once the opaque numbered envelope used for random allocation is opened and the clinician and participant know which appliance type (either 0.018-inch slot or 0.022-inch slot) will be used, the appliance will be clearly specified on the pro forma kept within the patient’s case notes. This will allow the clinician to adhere to the recommended standard archwire sequence for each type of appliance.

### Data and records to be collected

The following standardized data will be recorded for the trial participants at three stages of orthodontic treatment. Before start of orthodontic treatment: full orthodontic diagnostic clinical assessment, orthodontically trimmed study models at the start of orthodontic treatment, IOTN (aesthetic component score), long-cone paralleling technique periapical radiographs of maxillary central incisors, lateral cephalometric radiographs recorded before the start of treatment and patient questionnaire (pre-treatment). During orthodontic treatment: treatment duration, number of appointments, dates of key stages in fixed appliance orthodontic treatment, number of fixed appliance components replaced during active treatment, patient questionnaires (Smiles Better) regarding their perception of the impact of treatment (completed by the patient at six months from the start of orthodontic treatment), long-cone paralleling technique periapical radiographs of maxillary incisors recorded at nine months after the start of orthodontic treatment using digital radiography and lateral cephalometric radiograph recorded before the completion of active treatment.

End of orthodontic treatment: orthodontically trimmed study models at the end of treatment, patient questionnaire (post-treatment) and IOTN (aesthetic component score).

### Data management

A data collection sheet designed specifically for the current trial will be used to collect data from all participants’ records including study models, patient questionnaires, case notes and radiographs. The data collection sheet will be coded to allow for the blinding of the investigator to the type of appliance used during data analysis. The data will then be uploaded into a validated excel sheet specially designed for the current trial complying with Good Clinical Practice regulations. At the end of the trial the data will be exported into SPSS (Statistical Package for Social Sciences, Inc., Chicago, Illinois, United States) v.18 for statistical analysis.

### Post-trial care

All study documentation will be retained for at least five years post final data lock. The end of study is defined as the last participant’s last visit. The end of the study will be reported to the Research Ethics Committee (REC) within 90 days, or 15 days if the study is terminated prematurely. A summary report of the study will be provided to the REC within one year of the end of the study.

### Statistical analysis plan (SAP)

#### Descriptive statistics

Descriptive statistics for demographic data (such as age and gender) and baseline measurements will be tabulated by treatment group. Data will be checked for normality of distribution and any evidence of skewness.

#### Statistical analysis

Table 1 shows the planned statistical tests to be used for each variable investigated. The significance level will be set to α = 0.05 (two-tailed).

**Table 1 Tab1:** **Statistical tests**

Outcome measure		Type of variable	Statistical test ***P***<0.05
**Primary outcome**	Duration of alignment stage for the upper and lower arches	Continuous, assuming normal distribution	One-way ANOVA test
**Secondary outcomes**	Number of visits required	Continuous, assuming normal distribution	One-way ANOVA test
	Occlusal outcome PAR	Continuous, assuming normal distribution	One-way ANOVA test
	Patient perception	Categorical data	Chi-square test
	Severity of OIIRR	Categorical data	Chi-square test or Friedman test

A list of statistical tests that will be used for data analysis depending on the type of data in the current trial. Peer Assessment Rating index (PAR), orthodontically induced inflammatory root resorption (OIIRR), analysis of variance (ANOVA).

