**Methods/Design:**

This is a prospective, multicenter, randomized clinical trial, undertaken in the secondary care hospital environment in the NHS Tayside region of Scotland (United Kingdom). A total of 216 orthodontic patients will be recruited in three centers in secondary care hospitals in NHS Tayside. The participants will be randomly allocated to treatment with either the 0.018-inch or 0.022-inch bracket slot systems (n = 108 for each group) using Victory series™ conventional pre-adjusted bracket systems (3 M Unitek, Monrovia, United States). Baseline records and outcome data collected during and at the end of orthodontic treatment will be assessed. The primary outcome measures will be the duration of orthodontic treatment in the maxillary and mandibular arches. The secondary outcome measures will be the number of scheduled appointments for orthodontic treatment in the maxillary and mandibular arches, treatment outcome using Peer Assessment Rating index (PAR), orthodontically induced inflammatory root resorption (as measured using periapical radiographs) and the patient’s perception of wearing orthodontic appliances.

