#### Primary outcome

The primary outcome will be the duration of orthodontic treatment (measured in months) required to finish orthodontic treatment in both the maxillary and mandibular arches, including the number of visits required to complete treatment.

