### Target sample size

The sample size calculation is based on the primary outcome of duration of orthodontic treatment. Using nQuery Advisor 7.0 sample size was calculated to detect a difference in mean treatment duration of three months (clinically important difference). Standard deviation was estimated using the studies of Amditis and Smith [5] and Eberting et al. [12]. A sample size of 92 in each group will have 80% power to detect a difference in means of three months assuming that the common standard deviation is 7.2 using a two group Student’s *t*-test with a 0.05 two-sided significance level. Assuming a 15 to 20% dropout rate, we will recruit a total of 216 patients.

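### Table 1 makes alignment-stage duration the primary test, but the trial is defined and powered on total treatment duration, which has no planned test

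*Protocol article*

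**What the plan says.** Three places in the protocol article name the length of the whole treatment as the primary outcome:

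- Abstract, Methods/Design: "The primary outcome measures will be the duration of orthodontic treatment in the maxillary and mandibular arches".
- Primary outcome section: "The primary outcome will be the duration of orthodontic treatment (measured in months) required to finish orthodontic treatment". This covers both arches.
- Target sample size section: "The sample size calculation is based on the primary outcome of duration of orthodontic treatment". It continues: "A sample size of 92 in each group will have 80% power to detect a difference in means of three months". The SD behind this figure is 7.2.

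The Statistical analysis section then refers the reader to Table 1 for the test planned for each variable, at two-sided 0.05. The only row labelled primary in Table 1 reads "Duration of alignment stage for the upper and lower arches", to be tested by one-way ANOVA. The other rows are number of visits, PAR, patient perception and root resorption. Total treatment duration does not appear. The alignment stage is neither mentioned nor defined elsewhere in the text available.

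**The concern.** A stage of treatment is not the treatment. Followed literally, Table 1 tests a variable that was not declared primary and leaves the declared and powered outcome without a test.

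Three things are at stake:

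- **Power.** The target difference, SD and power were all set for total duration. They give no assurance about a test on one stage.
- **Interpretation.** A shorter alignment stage need not mean a shorter treatment. The Background ties the suggested slot effects (overbite reduction, space closure, torque) to the working stainless steel archwires, and the Intervention protocol places those wires last in each sequence. That these effects fall largely after alignment is our inference. The Background also suggests that the smaller slot may deliver torque sooner.
- **Choice after the data.** With two candidate primary outcomes in print, either could later be presented as the planned one. Clinician and patient both know the allocation, so the primary outcome needs to be beyond dispute.

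**Working it through.** **1. Are the two variables the same?** No. The section on data and records to be collected lists treatment duration and the dates of key treatment stages as separate items. The Primary outcome section runs to the finish of treatment, whereas Table 1 names one stage.

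**2. Does the stated sample size reproduce for total duration?** Inputs from Target sample size: difference δ = 3 months, SD σ = 7.2, two-sided α = 0.05, power 80%.

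- Normal approximation: n = 2(z₀.₉₇₅ + z₀.₈₀)²(σ/δ)² = 2 × (1.960 + 0.842)² × (7.2/3)² = 2 × 7.849 × 5.76 = 90.4, so 91 per group.
- Exact noncentral t: power is 0.7983 at 91 per group and 0.8026 at 92, so 92 per group. This matches the article.
- One-way ANOVA with two groups (noncentral F, 1 and 182 df): power 0.8026 at 92 per group. With two groups F = t², so naming ANOVA in one place and the t-test in another does no harm.

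The standardised effect is 3/7.2 = 0.417, and it belongs to total duration.

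**3. What power does the Table 1 test have?** It cannot be computed from the article, which gives no difference or SD for the alignment stage. To show how open it is, take 92 per group and *assumed* SDs. The difference detectable with 80% power is approximately σ × 2.802 × √(2/92) = 0.413σ. Power for an *assumed* 1-month difference is from the exact t:

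| Assumed SD (months) | Detectable difference at 80% power (months) | Power for a 1-month difference |
|---|---|---|
| 2 | 0.8 | 92% |
| 3 | 1.2 | 61% |
| 4 | 1.7 | 39% |
| 5 | 2.1 | 27% |

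**4. What does 3 months mean on each scale?** The Discussion puts fixed appliance treatment at about two years: 3/24 = 12.5%. For an alignment stage of 6 to 9 months (assumed), 3/9 = 33% and 3/6 = 50%. The same 3 months is a very different claim on the two scales.

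**5. What if either outcome could be claimed?** Two tests at 0.05 would give a chance of at least one false positive of 1 − 0.95² = 9.75% if independent. It would be lower if the two durations are positively correlated, as is likely when one is part of the other.

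**The case against.** The best reply is that this is a mislabelled cell. Three consistent statements name treatment duration, and the alignment stage appears once. The sample size section also mentions a two-group t-test on mean treatment duration, which with two groups is equivalent to the ANOVA in Table 1. On this reading nobody would be misled, and loss of the primary test is a risk rather than a certainty.

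Much of this is fair. A slip is a plausible explanation, and nothing in the design, data or sample size is wrong. But the t-test is named only as the basis of the sample size, while Table 1 is presented as the planned analysis. A prespecified primary test should not depend on guessing which of two statements was meant.

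Nor is this detail left to a fuller document: the article fixes the primary row and fixes it wrongly.

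Two limits stand. The 6 to 9 months and the alignment-stage SDs are assumptions, and the argument that slot effects arise late is an inference. The contradiction needs neither.

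It is also true that swapping the variable leaves open whether there is one duration or one per arch. That belongs in the correction.

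**Conclusion.** The concern holds, and Table 1 is wrong as written. Its primary row contradicts the abstract, the Primary outcome section and the sample size, and the outcome on which the trial was powered has no planned test. The 92 per group and 80% power are correct for total duration and say nothing about the alignment stage, whose power could lie anywhere from 27% to 92% for a 1-month difference under assumed SDs of 5 down to 2 months. Because the row decides which hypothesis the trial tests, it must be corrected before analysis. The contradiction rests on the text alone; only the illustrations of size rest on assumptions.

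**What to change.** Replace the primary row of Table 1 with total duration of fixed appliance treatment in months, keeping the both-arches scope of the Primary outcome section, and state its start and end. Bonding to debonding would serve: the Trial monitoring section already uses these points as its recording window for adverse events and equates debonding with the end of treatment. State whether this is a single duration per patient or one per arch.

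If alignment-stage duration is wanted, define its start and end and list it as secondary or exploratory; the recorded stage dates should supply it.

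While the row is open, settle the status of the number of visits, which the Primary outcome section folds into the primary outcome but the abstract and Table 1 treat as secondary.

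The main change costs one table row. It needs no new data, and the 92 per group stands.

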### Participant inclusion criteria

Patients scheduled to undergo dual arch fixed appliance orthodontic treatment in any of the three trial centers will be invited to participate in this trial by the operator planning to conduct their orthodontic treatment. Patients who are eligible to receive treatment in the NHS Scotland should have a significant need of treatment which requires an Index of Orthodontic Treatment Need (IOTN) score of 4 or 5 for the dental health component, or a score of 3 combined with a high aesthetic component score (>5) [11]. All types of malocclusions (Class I, II and III malocclusions) will be recruited to the study including cases which require extraction or non-extraction as part of the treatment plan.

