#### Secondary outcomes

The first secondary outcome will be the treatment outcome. This will be measured by evaluating the quality of treatment, the effectiveness of the appliance in delivering torque and the improvement in dental attractiveness. The quality of the treatment result will principally be measured by assessing the occlusal outcome using the Peer Assessment Rating Index (PAR Index) from study models recorded at the start and end of treatment. The torque of the maxillary incisors will be used to evaluate the effectiveness of appliance in delivering effective torque by measuring the angle between the long axis of the central incisors and the maxillary base from lateral cephalograms towards the end of treatment. The improvement in the dental attractiveness of the patient will be calculated using the aesthetic component of the IOTN. This will be evaluated by comparing the patient rating to the attractiveness of his or her teeth before and after treatment.

The second secondary outcome will be the biological side effects of the treatment, as measured by the amount of OIIRR. OIIRR will be established from periapical radiographs recorded at nine months into active treatment. Patients who show evidence of marked OIIRR will be treated in accordance with current recommendations.

The third secondary outcome will be the patient’s perception of wearing the fixed orthodontic appliance and of treatment outcome. This will be recorded using a questionnaire (Smiles Better) at six months after the start of treatment. Patient perception of the of fixed appliance treatment outcome will be measured by comparing patients’ pre-treatment and after-treatment questionnaires.

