### Sequence generation and randomization

Simple randomization will be accomplished with no stratification using a restricted (10 number block) random number using http://www.graphpad.com/quickcalcs/randomn2.cfm to ensure equivalence of numbers in each group. The odd numbers will be allocated to group 1 and the even numbers to group 2. In every 10 number block from the random table, the sequence will be checked to ensure the even numbers are equal to the odd numbers. Each number in the random table will be given a study number and assigned into one of the study groups. A table for the allocation of the participants in the study will be composed and kept in a sealed envelope. All the documents used for the randomization and allocation sequence generation will be kept in a box in a locked office away from the clinical environments.

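### Table 1 fixes an unadjusted one-way ANOVA for duration, visits and PAR although centre and baseline PAR are available: a valid test, but precision of unknown size is given up

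*Protocol article*

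**What the plan says.** Table 1 in the protocol article's Statistical analysis plan section names a "One-way ANOVA test" for the primary duration outcome, for number of visits and for occlusal outcome by PAR. No centre term, covariate or adjusted analysis is mentioned anywhere in the article. Under Descriptive statistics, baseline measurements are to be tabulated by arm; no other analytic role is given to them there.

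The setting is heterogeneous. Three NHS Tayside sites take part. Under Participant inclusion criteria, "All types of malocclusions (Class I, II and III malocclusions) will be recruited to the study including cases which require extraction or non-extraction". Under Sequence generation and randomization, "Simple randomization will be accomplished with no stratification"; blocks of 10 balance the arm totals only.

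Baseline information exists. Under Secondary outcomes, PAR is scored "from study models recorded at the start and end of treatment". Under Data and records to be collected, the pre-treatment set includes a full diagnostic clinical assessment and "lateral cephalometric radiographs recorded before the start of treatment".

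Target sample size uses the same unadjusted comparison: "A sample size of 92 in each group will have 80% power", for a 3-month difference with a common SD of 7.2, by a two-group t-test "with a 0.05 two-sided significance level".

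**The concern.** Neither the design nor the analysis does anything about centre or case severity. Randomisation does not balance them within strata, and a one-factor ANOVA leaves whatever outcome variation they explain in the error term. If they are prognostic for duration, visits or PAR, the confidence interval for the slot-size effect is wider than it need be. The estimate also carries chance imbalance that a model could have removed. The remedy uses data that the trial collects anyway, and the trial is sized with almost no margin over 80% power, so even a modest gain would be worth having.

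**Working it through.** **1. The test named.** With two arms, the one-way ANOVA F statistic equals the square of the two-sample t statistic. Table 1 and the sample size section therefore use the same unadjusted comparison.

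**2. Reproducing the plan's figure.** Inputs from Target sample size: difference 3 months, SD 7.2, two-sided alpha 0.05, power 80%.
- Normal approximation: n = 2 × (1.96 + 0.842)² × (7.2/3)² = 90.4, so 91 per arm.
- Noncentral t: 91.39, so 92 per arm, with power 80.3% at 92.

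The stated 92 per arm is reproduced.

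**3. Effect of adjustment.** Let R² be the share of within-arm outcome variance explained by the covariates. Then residual SD = 7.2 × √(1 − R²), and SE of the difference = residual SD × √(2/92). The documents give no R², no baseline–outcome correlation and no centre effect, so R² is an assumption shown as a range.

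| R² (assumed) | Residual SD | SE of difference (months) | 95% CI half-width (months) | Power at 92 per arm | n per arm for 80% |
|---|---|---|---|---|---|
| 0 | 7.20 | 1.06 | 2.09 | 80.3% | 92 |
| 0.02 | 7.13 | 1.05 | 2.07 | about 81% | 90 |
| 0.05 | 7.02 | 1.03 | 2.04 | 82.2% | 87 |
| 0.10 | 6.83 | 1.01 | 1.99 | 84.2% | 83 |
| 0.20 | 6.44 | 0.95 | 1.87 | 88.2% | 74 |
| 0.30 | 6.02 | 0.89 | 1.75 | 91.9% | 65 |

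**4. Cost if the covariates are useless.** Two centre indicators, baseline PAR and extraction use four degrees of freedom. At R² = 0, reducing the degrees of freedom from 182 to 178 changes power from 80.26% to 80.25%, about 0.01 percentage points.

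**5. PAR.** Let ρ be the correlation of start and end PAR (not given), with equal variances assumed at the two times. Relative to an unadjusted end score, the variance is 1 − ρ² with ANCOVA and 2(1 − ρ) with a change score.
- ρ = 0.2: 0.96 against 1.60.
- ρ = 0.3: 0.91 against 1.40.
- ρ = 0.5: 0.75 against 1.00.

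The gap is (1 − ρ)², which is never negative. So ANCOVA is at least as precise in large samples whichever PAR measure Table 1 intends.

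**6. What the figures describe.** The 3 months and SD 7.2 refer to total treatment duration in Target sample size, whereas the primary row of Table 1 names the alignment stage. The table in step 3 applies to total duration. The article gives no SD from which to compute it for the alignment stage.

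**The case against.** The strongest reply is that nothing is wrong with the stated test. Under randomisation it is unbiased and holds its type I error, and chance imbalance is already allowed for in its p-value and interval. The sample size was built on it, and since randomisation was not stratified, no stratification factor has been left out of the model. All of that stands. A reader might infer that the result will be biased by uneven case mix; the documents do not support this.

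The size of the gain is also assumed. At R² = 0.02 it is under one percentage point of power. That stands too.

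Three further inferences are tempting and should not be drawn:
- **That adjustment would win back power lost to dropout.** At 20% dropout, 216 × 0.80 / 2 is about 86 per arm, but that is a complete-case count. The section on intention-to-treat and imputation keeps everyone randomised and fills missing outcomes with the arm median, so the planned test runs on 108 per arm. Whether that imputation is sound is a separate question.
- **That every useful covariate is already recorded.** Centre and start-of-treatment models are certain. Planned extraction is not a listed data item; it is only implied by the diagnostic assessment and by the eligibility text on treatment plans.
- **That ANOVA is the stated test for incisor torque.** Torque has no row in Table 1, so no test is stated for it there.

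It may also be said that baseline PAR is used if the outcome is change in PAR. That is possible, but step 5 shows that ANCOVA would still be at least as precise. Finally, an article may leave covariates to a fuller plan. This carries less weight here, because Table 1 is presented as the list of planned tests and names this one.

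**Conclusion.** The point holds as a nearly free improvement in efficiency, not as an error of validity. Table 1 commits duration, visits and PAR to an unadjusted test while centre and baseline PAR are at hand in a mixed, unstratified, three-centre trial. On the sample size section's own inputs for total duration, the gain runs from under 1 percentage point of power (R² = 0.02) to about 12 points (R² = 0.30). It is nil if the covariates are not prognostic, and the loss in that case is negligible. These figures rest on an R² that the documents do not supply and on 92 analysable patients per arm. They also assume that the outcome tested is total treatment duration, not the alignment stage.

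**What to change.** Before the data are analysed by arm, replace the one-way ANOVA entries in Table 1 with a prespecified ANCOVA:
- **Duration and number of visits:** arm, centre and baseline PAR, plus planned extraction (yes/no) if the baseline diagnostic assessment records it.
- **End-of-treatment PAR:** arm, centre and baseline PAR.
- **Incisor torque, if it is to be tested:** add a row with arm, centre and the pre-treatment incisor angle measured on the baseline cephalogram.

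Keep the unadjusted comparison as a supportive analysis, so that the result remains linked to the sample size calculation. For centre and baseline PAR this costs a change of wording, with no new patients, visits or records. Extraction needs a check that it was recorded at baseline. The incisor angle needs a measurement on films already taken. The sample size need not change.

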## Methods/Design

### Trial design

The current trial is a multicenter, two-arm, parallel group, randomized controlled trial (Figure 1) designed following the CONSORT guidelines [10]. Patients who give informed consent to participate in this study will be entered into the study database, which will be held on one of the computers within the Orthodontic Department at Dundee Dental Hospital and School. Each participating patient will be allocated the next available study number at the start of active treatment using a series of opaque envelopes containing the treatment group.

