### Stopping rule

During the nine-month periapical radiographic assessment, if severe OIIRR (more than one third of the root Malmgren et al. [13]) is found in the majority of patients in one group, whilst the other group shows minor changes, then a trial monitoring committee will be convened to consider whether the study will be terminated.

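### Friedman's test is named as an option for root resorption severity, but it needs related samples and cannot compare the two independent arms

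*Protocol article*

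**What the plan says.** The Trial design section describes a "multicenter, two-arm, parallel group, randomized controlled trial", and the abstract gives "n = 108 for each group". Under Secondary outcomes, "OIIRR will be established from periapical radiographs recorded at nine months into active treatment". In Table 1 the row "Severity of OIIRR" is typed as categorical data and assigned a "Chi-square test or Friedman test". The table note says only that the tests depend on the type of data, and the row has already fixed that type.

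The Stopping rule section shows that resorption is graded. Its condition begins "if severe OIIRR (more than one third of the root" and is set against minor changes in the other arm.

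The section on data and records to be collected lists, before treatment, "long-cone paralleling technique periapical radiographs of maxillary central incisors" and, during treatment, "long-cone paralleling technique periapical radiographs of maxillary incisors recorded at nine months".

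**The concern.** The question put to this outcome is whether slot size affects resorption, which is a comparison between different patients. Friedman's test ranks related measurements within a block. The only blocks in this trial are patients, and slot size does not vary within a patient. One of the two named tests therefore cannot answer the question, and the two tests address different hypotheses with no stated rule for choosing.

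OIIRR is the only harm outcome given a test in Table 1, and the nine-month films can also trigger a review of whether the trial continues. If Friedman were used, a small p-value could show only that roots shorten during treatment, yet be read as a difference between slot systems.

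**Working it through.** **Inputs.** From the article: two independent arms; 92 evaluable patients per group (Target sample size); two-sided 0.05; severity graded. The article gives neither the number of grades nor their distribution, so every split below is an assumption.

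**The plan's own figure.** For a difference of 3 months and SD 7.2, n = 2 × (1.960 + 0.842)² × 7.2² / 3² = 90.4, so 91 per group by the normal approximation. The exact t calculation gives 79.8% power at 91 and 80.3% at 92. The stated 92 reproduces. It concerns treatment duration; no power is stated for OIIRR.

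**What Friedman would test.** With two related conditions the statistic reduces to (p − m)² / (p + m) on 1 degree of freedom, where p and m count the patients who worsen and improve. Arm does not appear in it.
- With 184 simulated patients, no arm difference and resorption over time in everyone, it rejected in 100% of 2,000 runs.
- Forcing the arms into blocks means pairing unrelated patients. For one illustrative table (30/35/20/5/2 against 18/33/25/10/6, 92 per arm), 5,000 arbitrary pairings gave p-values from 0.00008 to 0.47 from the same data.

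**What chi-square does.** With equal arms the statistic is the sum of (a − b)² / (a + b) over the grades. For the same table: 144/48 + 4/68 + 25/45 + 25/15 + 16/8 = 3.00 + 0.06 + 0.56 + 1.67 + 2.00 = 7.28 on 4 degrees of freedom, p = 0.122. Shuffling the grade labels leaves it at 0.122. The Wilcoxon-Mann-Whitney test, which uses the order, gives p = 0.009.

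**Power, 92 per arm.** The assumed control split is 30/40/20/8/2%. A proportional-odds shift divides each cumulative odds by the odds ratio (OR). At OR 2.0 the first is 0.30/0.70 = 0.429, halved to 0.214, giving 0.214/1.214 = 17.6%. The full shifted split is 17.6/36.2/28.0/14.3/3.9%.

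| Assumed pattern | Chi-square | Rank test |
|---|---|---|
| Five grades, OR 1.0 | 4.4% | 4.9% |
| Five grades, OR 1.5 | 18% | 33% |
| Five grades, OR 2.0 | 50% | 73% |
| Five grades, OR 2.5 | 78% | 93% |
| Four grades (30/40/22/8), OR 2.0 | 55% | 72% |
| Three grades (30/60/10), OR 2.0 | 52% | 63% |
| Two grades (70/30), OR 2.0 | 63% | 63% |
| Five grades, excess in the worst (30/40/12/6/12) | 66–68% | 7% |

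The first row shows that chi-square keeps its level. The last shows that neither test is better against every pattern. An unadjusted proportional-odds score test is equivalent to the rank test, so the right-hand column serves for both.

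**Films.** Maxillary incisors include the central incisors, so the two film lists overlap. The nine-month wording drops the word central. If lateral incisors are filmed then, no baseline film is stated for them.

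**The case against.** Three stronger readings are tempting, and the article supports none of them.

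- *Both planned tests are wrong.* Chi-square is a legitimate test of categorical data in two independent arms and holds its 5% level. Its loss of power depends on an assumed number of grades and an assumed uniform shift, the pattern that suits a rank test. With two grades nothing is lost, and with an excess confined to the worst grade chi-square is far better. That last pattern matters because severe resorption is the harm the Stopping rule section singles out. This part of the objection stands: an ordinal method is a recommendation, not the correction of an error.
- *The films cover different teeth at the two times.* They overlap, and the missing word may be loose drafting. A between-arm comparison at nine months does not need a baseline film of every tooth. The difference in wording matters only for change from baseline or baseline adjustment.
- *Several teeth per patient will be analysed as if independent.* Nothing says so. The only OIIRR count described, in the Stopping rule section, is of patients.

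In defence of Friedman, it could serve a within-patient question, such as change over time. The article states no such aim for OIIRR, and its stated comparison is between slot systems. Nor is this a detail left to a fuller plan: the article presents Table 1 as the planned test for each variable, so the row fixes the method.

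**Conclusion.** The point holds for Friedman's test. It is wrong as written for the between-arm comparison, and offering it as an alternative to chi-square without a rule leaves the hypothesis open. This follows from the design alone and rests on no assumed figures.

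The case for an ordinal method over chi-square is conditional. Under a proportional-odds shift with five assumed grades and 92 per arm, the gain is about 14 to 23 percentage points of power for odds ratios from 1.5 to 2.5. It is smaller with fewer grades and reverses when the excess lies only in the worst grade. The wording on films needs reconciling but does not undermine a nine-month comparison of arms. The consequence is limited to one secondary outcome.

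**What to change.** In the OIIRR row of Table 1, delete Friedman for the comparison of arms. If a within-patient analysis is wanted, state it separately with its own purpose. Name one between-arm test in advance, on one score per patient, and define how that score is formed.

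A sensible single choice is proportional-odds regression of the nine-month grade with the baseline central-incisor grade as covariate. Its downside is low power when the excess is confined to the worst grade, so also report the proportion with severe OIIRR by arm. Keeping chi-square alone would also be valid, at the cost of ignoring order.

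In the section on data and records to be collected, state which incisors are filmed at each time. If lateral incisors are filmed only at nine months, say that they have no baseline and how they will be used.

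The cost is one table row and one or two sentences. It needs no new films or patients and leaves the primary analysis unchanged.
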